### Cohort expansion study

The cohort expansion study will recruit a minimum of 21 and maximum of 36 babies to further assess the safety and PK of RP2D. The DSMB will convene after every 10 participants are enrolled to assess PK and the overall safety data.

It is anticipated that if the acetaldehyde data in the dose escalation study are reassuring, the expansion cohort will not include blood acetaldehyde levels as part of the PK blood analysis.

### Exploratory biomarker study

Exploratory blood marker studies are integral aspects to neonatal neuroprotection trials.^41^ Blood inflammatory cytokines,^42^,^44^ microRNA,^45^ neurospecific proteins^46 47^ and metabolomics^48 49^ have shown promise in predicting severity of HIE, 2-year neurodevelopmental outcomes and developing our understanding of the molecular pathways activated in babies with HIE. As brain injury is a temporal process, evolving with time, blood samples over several time points are necessary.

The exploratory biomarker study is an optional parallel study aimed to use the next generation of novel technology to identify promising biomarkers of HIE severity. Blood samples at recruitment, T0+24 hours, T0+48 hours, T0+72 hours and T0+96 hours will be taken to assess rapid point-of-care test (POCT) Ubiquitin Carboxyl-Terminal Hydrolase L1 (UCH-L1) and Glial Fibrillary Acidic Protein (GFAP),^50^ NUcleic acid Linked Immuno-Sandwich Assay (NULISA),^51^ micro-RNA, metabolomics and an extensive renal function panel (see figure 3).

**Figure 3 F3:**
[figure not shown]
Exploratory Biomarker Study in the Acute High Dose Melatonin for Encephalopathy of the Newborn (ACUMEN) Study. The optional exploratory biomarker study aims to use the next generation of novel technology to identify promising biomarkers of hypoxic-ischaemic encephalopathy (HIE) severity. This includes validating rapid POCT UCH-L1 and GFAP test for HIE. Plasma will also be assessed using NUcleic acid Linked Immuno-Sandwich Assay (NULISA), a novel, proteomic liquid biopsy platform with high attomolar sensitivity and high multiplexing to profile over 120 disease markers, metabolomics, microRNA and assessment of renal injury. Created in BioRender. [name] (2025) https://BioRender.com/ka7nocl.

### Study intervention and outcomes

#### Eligibility criteria

To account for differences in cooling criteria across different neonatal units, the trial is pragmatic and will include babies eligible for HT according to local guidelines. Clinical data including blood gas, neurological examination and background aEEG/EEG activity will be collected for analysis.

Baby admitted to the NICU with moderate/severe HIE meeting eligibility criteria for HT (in accordance with local guidelines) and:Born at ≥36 completed weeks gestation.Clinically stable* at the time of IMP administration.Invasive blood pressure monitoring in situ prior to the administration of the IMP loading dose.All participants will undergo a further assessment of HIE grade as determined by aEEG/EEG and/or a Modified Sarnat neurological examination prior to IMP administration.Sentinel Participant Criteria Only: must not meet the criteria for severe HIE.Informed consent from parents/guardians/person with legal responsibility.

*Definition of Clinical Stability

Eligibility of the participant must be rechecked prior to every IMP administration given the varying clinical status of these infants. Stability will take the following into consideration:

Well-placed central venous catheter or patent peripheral cannula in situ.Mean blood pressure (with or without inotropic support) must be greater than the fifth centile for gestation within 30 mins prior to IMP administration.Clinical or electrical seizures, if present, are controlled with antiseizure medications.Clinical observations within an acceptable range for an infant undergoing HT.No clinical stability concerns from the attending neonatologist.

#### Exclusion criteria

Baby >6 hours of age when IMP administered.Initiation of IMP is unlikely to be administered within 6 hours of birth.Infants born in very poor condition or judged too sick to be included (high risk of mortality) in an experimental first-in-human study, for example, infants that are requiring maximal intensive care therapy or in a condition considered to be life-limiting.Postnatal hypoxic insult without any evidence of HIE at birth.Birth weight less than the second centile for gestation on UK-WHO growth charts.Congenital anomalies, that is, any major antenatally diagnosed congenital abnormalities such as congenital heart disease, suspected or known chromosomal abnormalities.Head circumference less than second centile adjusted to sex of the baby on UK-WHO growth charts.Infant is participating or intends to participate in another interventioanl study during the birth hospitalisation (not including oservational studies).Parents/legal guardians unable to give consent due to leanring or other difficulties.

In the unlikely event of multiple births, if one baby has HIE, participation in the trial will be offered. If both/multiple babies have HIE, participation in the trial will not be offered.

### Recruitment and consent

The parent/legal guardian(s) of eligible participants will be identified by the clinical team on admission to the neonatal unit for cooling and asked for their willingness to participate in the trial. Informed consent will be obtained by a medically qualified investigator or authorised delegate of the study team. Given the time-critical nature of the trial and associated traumatic perinatal circumstances, a recruitment video and short patient information leaflet will be provided in addition to a more detailed patient information sheet. Verbal consent may be obtained initially, witnessed by an independent member of the clinical team, followed by written consent no later than 24 hours after birth. Separate consent will also be obtained for the optional biomarker study. Use of local language translation services to facilitate the consenting process in non-English-speaking parent/legal guardian(s) is permissive where the investigator is confident the discussion was accurately understood.

### Study intervention

The IMP, melatonin in ethanol 50 mg/mL solution for infusion, is a clear solution presented in 6 mL sterile amber vials, manufactured in accordance with GMP by Eurofins Proxy Laboratories under their manufacturing authorisation licence. Orphan drug designation has been obtained for HIE with the European Medicines Agency (EU/3/23/2757) and the US Food and Drug Administration (DRU-2022–8888). The solution is stored at 2°C to 8°C and requires dilution in 5% glucose to a final melatonin concentration of 2 mg/mL (3.8% v/v ethanol) for intravenous use. The IMP should be started as a 2-hour infusion within 6 hours of birth (T0) via a separate lumen of a well-placed central venous catheter or peripheral 24G cannula. Subsequently, five maintenance doses will be administered every 12 hours from T0+24 hours over 2 hours. Clinical stability (as stated in the eligibility criteria) must be assessed and confirmed prior to each IMP administration. Where the baby is not stable at assessment but subsequently becomes stable within 1 hour of the scheduled dosing event, the IMP may be delivered. Where a dose was missed due to clinical instability, the next IMP dose must be administered in accordance with the treatment schedule. No extra IMP doses outside the treatment schedule will be allowed.

### Criteria for discontinuing or modifying interventions

Any discontinuation or modification of doses will be in line with the trial design and in accordance with the dose escalation procedure confirmed by the DSMB and TSC. Reasons for discontinuing treatment include:

Serious Adverse Event (SAE) or “severe” AE, that is, grade 3 and above on the Neonatal Adverse Event Serverity Scale (NAESS)^39^ considered related to IMP (definition of suspected DLE)PK exposure cap of melatonin (<33.5mg/L), ethanol (<0.25g/L) or acetaldehyde (<2.2mg/L) exceeded (this will be available concomitantly in the *sentinel* baby only). PK exposure cap of melatonin, ethanol or acetaldehyde predicted to exceed at the subsequent dose escalation.Withdrawal of consent by parent/legal guardian(s).A decision made by the treating clinician based on any change in the infant’s condition that justifies the discontinuation of treatment.

The analysis will be by intention to treat. Participants who discontinue protocol treatment, for any of the above reasons, should remain in the trial for the purpose of follow-up and data analysis. A blood sample will be collected at the time of termination and an additional sample 24 hours after the last IMP administration. These samples will be analysed for PK purposes to characterise the plasma levels of melatonin and ethanol.

### Concomitant care

Melatonin is metabolised by the hepatic cytochrome P450 CYP1A enzymes, primarily CYP1A2; therefore, interactions between melatonin and other active substances as a consequence of their effect on CYP1A enzymes are possible. Administration of CYP1A2 inhibitors (eg, allopurinol, ciprofloxacin, amiodarone) to ACUMEN participants should be avoided, where possible. The sponsor will collect a list of all concomitant medications given to participants on the concomitant medications log. The IMP treatment will be administered alongside standard neonatal neurocritical care for babies receiving HT for HIE. These include:

Continuous aEEG/EEG.Cerebral near infrared spectroscopy (NIRS).MRI and proton (^1^H) MRS on days 4–10 (preferred timing days 4–6)

### Amplitude-integrated electroencephalography /electroencephalography (aEEG/EEG)

Continuous aEEG/EEG will be initiated prior to IMP administration and continued for 24 hours after rewarming. For the ACUMEN Study, a full neonatal aEEG/EEG recording will be collected using the Stratus NICU EEG system (Stratus EEG software version 5.1.3). Time to recovery of aEEG/EEG background activity and sleep wave cycling accurately predicts adverse neurodevelopmental outcomes at 18 months (positive predictive value (PPV)=96.2%, negative predictive value (NPV)=88.92%, and PPV=88.5%, NPV=82.4%, respectively).^26^ In addition, seizure detection and prompt treatment is essential given that up to 50% of HIE infants develop seizures,^52^ with ~20% occurring during rewarming.^53 54^

### Cerebral NIRS

NIRS monitoring provides insight into regional tissue oxygen saturation (rSO_2_), indicating the balance between oxygen delivery to tissues and tissue oxygen utilisation at the bedside. The ACUMEN Trial will collect NIRS data over the period of cooling and rewarming using the Masimo Root with the O3 Regional Oximetry system. In HIE,^55^ elevated cerebral regional oxygen saturation (CrSO_2_) within 6 hours of birth,^56^ during cooling^57 58^ and rewarming,^58 59^ correlates with adverse neurological outcomes.

### MRI/magnetic resonance spectroscopy (MRS)

Conventional MRI provides information regarding the nature and severity of the insult, timing and prognosis. This is implied by the location and extent of injury and the signal characteristics on T1-weighted (T1W), T2-weighted (T2W) and diffusion-weighted MRI (dMRI). For optimal detection of evolving injury with dMRI, the scan should be acquired within the first 10 days after birth prior to pseudo-normalisation, with the optimal days of acquisition between days 4 and 6.^60 61^ Conventional MRI with dMRI predicts adverse neurodevelopmental outcomes at 2 years following HIE with a high degree of accuracy (Area under the Receiver Operating Characteristic (ROC) curve of 0.89 to 0.91).^62^ An imaging contract research organisation (CRO) (Bioxydyn) will assist with harmonisation of the multivendor 3T MRI scanners (Philips, Siemens and General Electric (GE)) using MRS and dMRI phantoms to ensure reproducibility and standardisation of MRS and dMRI. Data acquisition and analysis will meet regulatory expectations (International Council for Harmonisation (ICH) Good Clinical Practice (GCP)) with a controlled and auditable workflow.

Conventional MRI scans will be reported by the local radiological team and used for routine clinical management and counselling at each site. In addition, conventional MRI scans (including T1W, T2W, dMRI, susceptibility weighted imaging (SWI) and magnetic resonance venography (MRV) sequences) will be pseudonymised and sent to Bioxydyn from where they will be forwarded to two independent neonatal neurologists with extensive experience in assessing neonatal MRIs, who are members of the ACUMEN consortium. MRIs will be scored using the validated Rutherford^63^ and Weeke^62^ Scores. At this stage, the scores will be blinded, but the dose escalation level will be known. These scores will be used throughout the phase 1 study for safety monitoring and will be part of the data assessed by the DSMB at each dose level. At the end of the study, the MRIs will be batched for final radiological scoring, when the assessors will be blinded, including blinding to the IMP dose level administered. Incidental findings are likely to have been picked up by the site clinical radiologist as part of standard care. Unexpected MRI findings that could be related to the IMP will be reported to the DSMB.

The MRS Lac/NAA peak area ratio acquired from the left BGT voxel using a long echo time (TE 288 msec) has a high predictive accuracy with a sensitivity and specificity, respectively, of 100% and 97% for motor outcome, 90% and 97% for cognitive outcome, and 81% and 97% for language outcomes using a Lac/NAA threshold of 0.39.^28^ The Lac/NAA peak area ratio has been used as a surrogate outcome measure in a phase 2 imaging biomarker neuroprotection trial for HIE^7^ and validated against 2-year neurodevelopmental outcomes.^64^ The Lac/NAA is currently the best available, pragmatic predictor of 2-year neurodevelopmental outcomes.^28 29^ The use of a robust surrogate imaging biomarker such as MRS Lac/NAA has the potential to expedite clinical translation by evaluating treatment effects in a timely fashion with smaller sample sizes. Developing a strong infrastructure for a high standard of MRI/MRS harmonisation in the ACUMEN Study will be vital for the success of future phase 2 surrogate imaging biomarker neuroprotection trials.

dMRI data will be processed to derive peak width of skeletonised mean diffusivity and fractional anisotropy. These are image markers of white matter microstructure based on diffusion tensor imaging, skeletonisation of white matter tracts and histogram analysis.^65^ The processing pipeline has been optimised for neonatal dMRI data^66^ and is suitable for analysing data acquired at multiple sites.^67^

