The DSMB will review the safety and PK data following the recruitment of the third baby in a cohort. The DSMB will recommend to the Trial Steering Committee (TSC) one of the following possible outcomes: (1) Recruit at the next dose level, (2) Continue recruitment at the current dose level, (3) Reduce dose to one of the previous dose levels (where relevant), or (4) Stop the trial. Dose escalation decisions will be based on both the concurrent accumulating safety (suspected DLEs) and PK data, and their predictions at the next dose level. For PK, the trial pharmacologist will develop a population-PK model to simulate the plasma melatonin levels and BACs at the next dose level. If PK modelling predicts that melatonin systemic exposure will be equal to or exceed the Cmax of 33.5 mg/L and Area under the serum concentration vs. time curve for 0-24h (AUC24) of 454.7 mg*h/L or the BAC safety threshold (<0.25 g/L), that dose level will not be opened to recruitment. For DLE predictions, a Bayesian Escalation with Overdose Control (EWOC) approach will be used. EWOC uses a statistical model to estimate the risk of DLE per dose level with the target level of DLEs set at 33% for this trial. While awaiting dose escalation decisions (from the second dose level onwards), and in the absence of DLEs in the first three babies, a maximum of three further babies can be recruited to the current dose level after approval from the DSMB. In the event of a DLE, or having recruited the three additional babies, backfilling^40^ to the previous dose level can occur while awaiting the dose escalation decision. Data acquired from additional babies will be included in a subsequent dose escalation report for review by the DSMB/TSC. Backfilling will be limited to a maximum of 15 babies in the dose escalation study.

The subsequent dose escalation will proceed to dose level 2 at a loading dose of 10 mg/kg and maintenance doses of 5 mg/kg. Subsequent doses for dose level 3 and dose level 4 will be determined by the safety and PK model prediction. Provided that dose levels 1 and 2 have not exceeded the maximum BAC safety threshold and no other dose-limiting toxicity is encountered, further escalation will be recommended. Using the parameters of a population PK model, dose escalation will be evaluated. The possible scenarios are:

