### Data collection and management

Participants meeting the eligibility criteria for the ACUMEN Trial will be enrolled via the Sealed Envelope online system, which will allocate participants to an individualised participant identification number (PIN) for pseudo-anonymisation of research data. During the dose escalation phase, assignment to the current dose level will be managed via the Sealed Envelope system in accordance with the dosing schedule approved by the TSC. Clinical data from participant records will be collected as illustrated in the schedule of events (see table 2) under the PIN into the password-protected study database (OpenClinica). MRI/MRS Digital Imaging and Communications in Medicine (DICOM) data will be transferred to VoxelFlow software, anonymised and reviewed by two independent experts in perinatal brain MRI interpretation. The aEEG/EEG recording will be uploaded to the Stratus EEG system software for review by a neurophysiologist with expertise in neonatal neurology. Where available, the NIRS trace will be transferred to the UCL Data Safe Haven for review. Laboratory data (including PK) will be provided directly to the sponsor. All PK final reports will be entered into OpenClinica linked to the PIN.

All data will be handled in accordance with the Data Protection Act 2018 and the EU General Data Protection Regulation (GDPR) 2016. The data are stored on secure, GDPR-compliant, cloud-based servers held within the UK and EU. Any transfer of documentation containing personally identifying data between the site and the coordinating centre will be subject to AES-256 industry-standard encryption.

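### The interim MRI scores shown to the DSMB are called blinded although the dose level is known, and the readers do not need the dose to score a scan

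*Protocol article*

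**What the plan says.** The section on MRI/magnetic resonance spectroscopy describes two rounds of expert scoring of the conventional MRI, both separate from the local clinical report.

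- **Interim round.** Pseudonymised scans go to the imaging CRO and are then "forwarded to two independent neonatal neurologists with extensive experience in assessing neonatal MRIs, who are members of the ACUMEN consortium". Of these scores the text says: "At this stage, the scores will be blinded, but the dose escalation level will be known". On their use it says: "These scores will be used throughout the phase 1 study for safety monitoring and will be part of the data assessed by the DSMB".
- **Final round.** At study end "the MRIs will be batched for final radiological scoring, when the assessors will be blinded, including blinding to the IMP dose level administered".

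The section on data collection and management describes a single review, with images "anonymised and reviewed by two independent experts in perinatal brain MRI interpretation". It does not say whether the same people carry out both rounds.

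**The concern.** The trial is an uncontrolled dose escalation, so the dose level is the main treatment information a scan reader could be masked to. A score described as blinded while the dose is known therefore leaves it unclear what has been masked and from whom.

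Rutherford and Weeke scores are assigned by a reader's judgement. A reader who knows that a baby received a higher dose may look harder for injury, or may discount it, so the direction of any bias cannot be predicted. The readers are called independent but belong to the consortium, which makes masking more valuable.

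The scores have a stated use: the DSMB sees them at each dose level. With cohorts of three, one or two scores coloured by expectation could alter the impression a dose level makes. This is a first-in-human study in newborns, where that impression matters. The DSMB needs the dose to interpret the scores; the reader does not need it to produce them.

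**Working it through.** The plan gives no figure to reproduce, and no power or error-rate formula applies. The check sets the relevant places side by side and adds simple proportions for scale.

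**1. Who knows the dose at the interim read?** The interim sentence does not name the person to whom the dose is known. The final read is introduced by contrast: there the assessors are blinded, and the text adds that this now includes the dose level. That addition would be unnecessary if the readers had been masked to dose before. The natural reading is that interim readers know the dose. Another reading, that only the DSMB knows it, is possible but less likely. Either way the wording does not settle the point.

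**2. Where do the interim scores go?**

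| Route | Place in the protocol article | Do the MRI scores enter? |
|---|---|---|
| DSMB data at each dose level | MRI/MRS section | Yes, stated |
| RP2D, through consideration of the safety data as a whole | Outcomes | Possible |
| Escalation decisions: "Dose escalation decisions will be based on both the concurrent accumulating safety (suspected DLEs) and PK data" | Dose escalation procedure | Not named as an input |
| EWOC model | Sample size and statistical analysis | No; it uses DLE occurrence |
| PK caps | Dose escalation procedure | No |
| Whether an event counts as a suspected DLE | Dose-limiting events | Judged by the treating neonatologist and site investigator, then reviewed independently; the MRI readers have no stated part |

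The scores can therefore influence judgement but do not enter the formal escalation rules.

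**3. How many babies are concerned?** From the trial design section:

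- Escalation phase, where dose varies: 24/60 = 40% to 39/60 = 65%.
- Expansion phase, all at the one RP2D: 21/60 = 35% to 36/60 = 60%.

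A bias that differs between dose levels therefore concerns mainly the escalation scans. These percentages give the share of babies in the phase where dose varies. They do not measure bias.

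**4. Would masking achieve anything when dosing is sequential?** At dose level 1 there is nothing to mask, because no other level is in use. From dose level 2 on, babies may be backfilled to the previous level, up to 15 in all. With a maximum of 39 escalation babies, backfill could reach 15/39 = 38% of them. In those periods scans from two dose levels can reach the readers close together, and calendar time alone does not reveal the dose.

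**5. Is masking practicable?** Scans already pass through the CRO in pseudonymised form. Dose assignment is held in the enrolment system. The trial statistician already prepares dose-level estimates for escalation decisions. The dose can be attached to a score after the score has been recorded.

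**The case against.** The strongest case on the other side has four parts.

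- **The wording is coherent as two stages.** Readers could first be masked to other information and then, at the end, to dose as well. That reading is possible, but the article does not say what is masked at the first stage, and the dose would still be known to the readers. This answers the charge of contradiction and leaves the design choice open to question.
- **The consequence is small.** Formal escalation rests on suspected DLEs and PK. The imaging measure the article stresses is the quantified Lac/NAA ratio, not the visual scores. This stands, and it limits the weight of the point.
- **Readers can guess the dose.** Recruitment runs level by level, and a consortium member scoring in real time will often infer it. This stands in part: backfilling weakens the inference, and a guess is less direct than a label.
- **The final read is protected.** A reader might infer from the interim disclosure that the final read is not truly blind. The document does not support that. It plans a batched read with assessors masked to dose, and does not say that the interim readers return. By the planned timeline, a six-month expansion phase separates escalation from the end of the study. The final read would be compromised only if the same people did both reads and could recall a scan's dose. Details of reader assignment and re-coding are what an article may leave to a full protocol or imaging charter, neither of which is shown.

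**Conclusion.** The point holds in a limited form. The article describes the interim MRI scores as blinded and in the same sentence says the dose level will be known. On the natural reading, scores that the DSMB uses at each dose level are assigned by consortium readers who know the dose, for no stated reason. That leaves an avoidable route for bias into safety judgement and, through the safety data as a whole, into the choice of RP2D. The size and direction of the bias cannot be derived from the document.

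Three stronger inferences should not be drawn.

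- The final read is not shown to be unblinded.
- The 40–65% figure is the share of babies in the phase where dose varies. It is not an established share of scans re-read by assessors already exposed to dose, because that would require the same readers in both rounds.
- The article does not tie the Rutherford or Weeke scores to its exploratory dose-response objective.

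The conclusion assumes that the dose is known to the interim readers. If it is known only to the DSMB, what remains is a sentence that needs correcting.

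**What to change.** In the MRI/MRS section, replace the clause that discloses the dose level with text to this effect: *Interim readers receive pseudonymised scans from the imaging CRO without dose or cohort labels. The trial statistician links the recorded scores to dose level, for the DSMB only.* State what else, if anything, the interim readers are masked to.

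For the final batched read, state whether the readers are the same. If they are, present the scans under new identifiers and in random order.

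The cost is minor: a change to the CRO transfer instructions, a linkage step for the statistician and, where the same readers return, re-coding of the scans. No extra scan or reader is needed. The gain is partial, because readers may still infer the dose from calendar time, above all at dose level 1.
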